#### COPD assessment

International studies have found high acceptance of spirometry within LCS programmes (>90%)^39,40^. We conservatively estimate that 400 (80%) of our LCS participants will consent to COPD assessment. Of these, we assume at least 200 (50%) will meet the criteria for a COPD diagnosis, for whom we can assess changes in baseline management after sending the report to the GP. Some improvement in COPD management over time may be expected following a spirometry test simply due to (normal) ongoing management by their GP or by the Hawthorne effect from being included in the study and having a spirometry test. We expect this to seen in about 10% of patients and if the proportion with improvements is significantly greater than 10%, then this might be attributable to the effect of the reporting and management recommendations that we will be providing to the GP. With a sample of 200 the study has 85% power to detect that a measured improvement in management is significantly greater than 10% when the actual proportion is 17% or more (95% significance level). Descriptive analysis of quantitative data will include frequency distributions (categorical and ordinal data); mean values for normally distributed numerical data; and median, minimum and maximum values and interquartile ranges for non-normally distributed numerical data. Comparison across subgroups of interest (e.g. GOLD classification, age, gender) will involve chi-square analysis for categorical variables; t-tests or analysis of variance for normally distributed or log transformed continuous variables; and the appropriate statistical test (e.g. Wilcoxin rank sums scores and Kruskal-Wallis tests) for non-normally distributed numerical data. GP’s COPD management variables (e.g. medications prescribed) at baseline and 4 months after sending repots to GPs will be categorised according to their consistency with COPD-X management recommendations for participant’s GOLD classification (Yes-fully, yes-partially and no). Each participant will be classified as having had improved management if the assessment changes from either: no to yes-fully or yes-partially; or from yes-partially to yes-fully. Wilson confidence limits will be calculated on this proportion and it will be tested for significance (one sample proportion test) versus the expected improvement proportion of 10%.

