Our study provides a feasible and efficient opportunity for diagnosing and assessing COPD severity among study participants. There are a number of key barriers^22^ to COPD diagnosis in primary care including the availability, training requirements and quality of spirometry. Including COPD in LCS programmes is an opportunity to improve the diagnosis and management of COPD. Two recent LCS programmes incorporating routine spirometry for individuals of predominantly lower socio-economic status in the United Kingdom reported that between 37-57% of eligible screening participants had airflow limitation consistent with COPD, and 50-70% of those were undiagnosed^39,40^. Among the 2,541 current or former smokers aged 55-74 years residing in three deprived areas of Manchester who were involved in the community-based LCS programme undertaken in that city, spirometry was successfully performed among more than 99% of attendees^40^. Furthermore, in the treatment arm of the Lung Screen Uptake Trial undertaken in deprived areas of London among current or former smokers aged 60-75 years, spirometry was performed in around 98% of participants^39^. There are other international LCS studies that have incorporated spirometry for less high-risk populations. The nested sub-study of COPD within the LCS trial is likely to further improve the cost-effectiveness of the screening pathway.

Once diagnosed, good management of COPD in primary care is important. Best practice management of COPD can slow progression, prevent exacerbations, and mitigate the impacts of this condition^1,33,41,42^. The key features of high-quality evidence-based COPD primary care are: 1) diagnosis through spirometry accompanied by assessment of the severity of COPD symptoms; 2) pharmacotherapy according to the severity of the COPD with the goal of maximising the person’s function together with regular re-assessment of COPD severity and review of medications; 3) prevention of acute exacerbations and early management of acute exacerbations when they occur; 4) non-pharmacological strategies such as the provision of COPD action plans and strategies for managing dyspnoea, self-management education and support, encouraging exercise, referral for pulmonary rehabilitation, and referral to community support groups; 5) smoking cessation support for those that continue to smoke; and 6) maximising management of co-morbid conditions such as cardiovascular disease, diabetes, anxiety and depression^43^.

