#### Incidental findings

Incidental findings are defined for the purposes of this study as any abnormalities or diseases identified on the CT scan other than lung cancer or lung nodules. It is expected that screening will detect incidental findings. Table 2 outlines categories of incidental findings, required action and follow-up to ensure action was undertaken.

Table 2: Categorisation of incidental findings, actions required and follow up

| **Category** | **Required action** | **Follow up** |
| --- | --- | --- |
| 1: major findings that may be life threatening and direct referral to hospital is required | Direct referral to hospital by radiologist or, if the participant is not on-site the radiologist will call the participant’s GP | Research nurse to call radiologist/GP to ensure referral done immediately |
| 2: significant findings (e.g. significantly dilated aortic aneurysm) requiring urgent referral | Urgent referral by participant’s GP | Research nurse to liaise with GP to ensure referral done within two weeks after report is issued |
| 3: findings indicative of cancer at another site (e.g. breast) or ctDNA information, after validation in a clinical grade test, requiring urgent referral; | Urgent referral by participant’s GP in liaison with oncology / respiratory specialists on project team. |  |
| 4: other non-cancer findings requiring non-urgent referral to primary or secondary care (e.g. significant fibrotic interstitial lung disease, TB, bronchiectasis) | Treatment by GP or non-urgent referral (by GP) to tertiary care | Study nurse to follow up on referrals in Éclair one month after report is issued |
| 5: non-cancer findings that may require management in primary care (e.g. COPD, ectatic aorta, coronary calcification) | Management by GP | Study co-ordinator to call GP to ensure patient has been seen |
| 6: findings that are usually not directly associated with a beneficial intervention (e.g. bronchial wall thickening) | No management required |  |

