### CT scan result management and follow up

#### Communication to participants and their whānau

In the GP arm, the GP or practice nurse will discuss the results of the scan with the participant and their whānau. For participants with clear or negative scans, this will involve a phone call from the nurse. With more complex results, the participants will be invited back to the practice for a discussion with the GP (at no cost to them). Should further scans or diagnostic investigations be required, the GP will refer the participant to the relevant tertiary service.

In the centralised arm, if no follow up is required, then the study nurse will contact the participant to inform them of the result. For participants with positive scans, the participant’s GP will contact the participant to arrange an appointment to discuss their results, and to arrange follow up (interval) CT scans and referrals for diagnostic investigations, with support from the study respiratory physician.

In both arms, participants will again be taken through their options, using a shared decision making process. Participants will always have a choice in the types of investigations they undertake and / or treatment they receive and are able to choose to decline if they wish.

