#### Referral for specialist assessment

In addition to the provision of information to their GP, the ADHB COPD health pathway will be used to determine if participants with moderate or severe COPD (GOLD classification B, C and D) should be referred for specialist assessment at their local respiratory clinic. [name] will review results for all participants with GOLD B, C, or D classifications to confirm if referral is required.

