### Smoking cessation advice

All participants who are current smokers will be provided with brief advice to quit, offered nicotine replacement or other pharmacological treatments to support smoking cessation, and offered referral to quit services. For participants whose calculated risk means they are not eligible for lung cancer screening this will be provided at the completion of the risk assessment process. Participants who are eligible for screening but choose not to proceed with a CT scan will receive this (brief advice to quit, offers of medications and referral to cessation services) at that decision point. Participants who proceed to screening will be offered this when they are given their results. All relevant staff will receive training in smoking cessation support, and DHB and PHO smokefree services are aware of the project and are supportive.

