## Ethical considerations

### Informed consent

Informed consent will be sought from all practices and participants involved in the trial. PHOs will provide agreement and clinical approval to join the study. Practices will choose to participate in the study and agree to conduct the study procedures including training, result management and risk assessment (for primary care arm). Consent for participation will be taken by a suitably trained clinician or researcher who is familiar with the risks and benefits of the process.

Consent from participants will use a two-step process; verbal consent to participate in the trial will be sought from people on the list of people who are potentially eligible for the trial and for risk assessment. Eligible participants who decide to undergo a CT scan will be asked to provide written consent for the scan prior to undergoing it. Those who undergo COPD assessment will provide separate written consent. At the same time, separate consent will be sought for a member of the research team to contact the person’s GP to collect data about what actions the GP clinic has taken after receiving the result (patient notification), and to collect data about follow up CT scans, and diagnostic procedures done following the screening CT scan (GP and hospital records).

For the COPD sub-study, explicit consent will be sought to access data collected as part of the main LCS study that are relevant for this study: demographic data (age, gender, ethnicity), co-morbid conditions and smoking data (current smoking status, smoking history including duration and intensity of smoking). Explicit consent will also be sought to access both primary care records and hospital records for the following information: Documentation of COPD and COPD-related diagnoses (emphysema, asthma, chronic bronchitis, bronchiectasis); previous spirometry results; primary care management of COPD including non-pharmacological management and prescribing of medications for COPD and/or related diagnoses (short and long acting anti-muscarinic agents, short and long acting beta agonists, inhaled corticosteroids, oral glucocorticoids, and antibiotics for respiratory symptoms) in the previous 12 months; and the number of acute exacerbation of COPD, GP consults for respiratory symptoms, ED visits or hospitalisations for COPD/respiratory conditions in the last 12 months.

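### The COPD management test points a significant excess over 10% to the GP letter, although other prompts the trial sets up in the same period are in neither the benchmark nor the interpretation

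*Protocol*

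**What the plan says.** The test is set out in the Protocol, Statistical Consideration and Data Analysis, COPD assessment. On numbers, "we assume at least 200 (50%) will meet the criteria for a COPD diagnosis". Each participant's GP management is graded no, partially or fully consistent with the COPD-X recommendations, at baseline and 4 months after the report goes to the GP. Any upward move counts as improved. The proportion improved is tested against 10% in a one-sample test. The 10% is explained by ordinary GP follow-up and a Hawthorne effect of being in the study and having spirometry. The interpretation follows: "if the proportion with improvements is significantly greater than 10%, then this might be attributable to the effect of the reporting and management recommendations" (those which the study sends to the GP).

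Other sections add care that can bear on the same outcome:

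- **Incidental findings, Table 2, category 5.** COPD is a named example of a CT finding for GP management. The follow-up entry is "Study co-ordinator to call GP to ensure patient has been seen".
- **Referral for specialist assessment.** Besides the information sent to the GP, a named reviewer "will review results for all participants with GOLD B, C, or D classifications to confirm if referral is required".
- **Smoking cessation advice.** Current smokers are given brief advice, "offered nicotine replacement or other pharmacological treatments to support smoking cessation, and offered referral to quit services". Those who are scanned receive this with their results. Results of COPD assessment (Participants) also has the nurse give brief advice and offer help to quit.
- **CT scan result management and follow up, first subsection.** On who gives the scan results, the text reads "In the GP arm, the GP or practice nurse will discuss the results of the scan with the participant and their whānau".

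The background section on COPD lists "smoking cessation support for those that continue to smoke" among the features of good COPD primary care. Informed consent seeks access to records of "primary care management of COPD including non-pharmacological management and prescribing of medications for COPD".

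**The concern.** In an uncontrolled before-and-after comparison, the benchmark has to carry everything that would have moved the outcome without the component of interest. Here the component named is the report and recommendations to the GP. The benchmark was set for two other influences only. The trial's own further prompts, above all a study call to the same GP about the same disease, sit outside it.

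If those prompts move even a modest share of participants up one grade, the test becomes significant and the one explanation the Protocol offers is the letter. A later programme might then adopt a results letter alone, expecting a gain that came partly from phone calls, specialist-referral review or cessation contacts.

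**Working it through.** **Inputs from the Protocol's statistical section on COPD assessment.** n = 200, benchmark p0 = 0.10, alternative p1 = 0.17, 5% significance level (sidedness not stated), stated power 85%.

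**Step 1: reproduce the stated power.** Two-sided 5%, one-sample z-test:

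- Standard error under the benchmark: √(0.10 × 0.90 / 200) = 0.0212.
- Standard error under the alternative: √(0.17 × 0.83 / 200) = 0.0266.
- Power = Φ[(0.07 − 1.96 × 0.0212) / 0.0266] = Φ(1.07) = 85.8%.
- Binomial power of the same test at its cut-off is 85.0%.

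The stated 85% is right for a two-sided 5% test. A one-sided 5% z-test would give 90.7%.

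**Step 2: find the cut-off.** The test rejects upward above 0.10 + 1.96 × 0.0212 = 0.1416, or 28.3 of 200, so at 29 or more (14.5%). The benchmark expects 0.10 × 200 = 20. Nine further improvements are enough.

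**Step 3: what the benchmark and interpretation cover.**

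| Source of change | In the 10%? | In the interpretation? |
|---|---|---|
| Usual GP management | Yes | As background |
| Study inclusion and spirometry (Hawthorne) | Yes | As background |
| Report and recommendations to the GP | No | Yes, the only cause named |
| Co-ordinator's call about COPD on CT | Not named | No |
| Review of GOLD B, C, D for specialist referral | Not named | No |
| Trial-mandated cessation support, if scored | Not named | No |

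On timing, baseline management is taken from the 12 months before assessment. Spirometry and CT are on the same visit, and the scan is reviewed within a few days. Table 2 gives no date for the category 5 call, but it follows the CT report. These prompts can therefore fall between the two gradings.

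**Step 4: chance of a positive result if the letter does nothing.** Take the 10% background as true and add d points from other trial care. The Protocol gives no value for d, so a range is shown. P(X ≥ 29) with X ~ Binomial(200, 0.10 + d):

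| d (points) | Extra improvements in 200 | P(significant) |
|---|---|---|
| 0 | 0 | 2.7% |
| 1 | 2 | 7.5% |
| 2 | 4 | 16% |
| 3 | 6 | 29% |
| 5 | 10 | 61% |
| 7 | 14 | 85% |
| 10 | 20 | 98% |

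Read as one-sided 5%, the z-test cut-off falls to 27 and the chances at 2, 5 and 7 points rise to 29%, 75% and 92%.

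At 7 points, other trial care would produce a significant result as often as the effect the sub-study was sized to detect.

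**The case against.** Four points on the other side deserve weight.

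1. **The wording is conditional.** The Protocol says an excess might be attributable to the report; it does not assert that it is. That stands. Even so, the letter is the only cause offered for an excess, and the alternatives considered omit the trial's own prompts.
2. **The outcome is the GP's management, with medications prescribed as its only example.** A reader might infer from the background list and the consent section that cessation support is scored. No passage says so. The first describes good care, the second the records to be accessed, and a detailed item list may sit in the statistical analysis plan. The cessation route is therefore conditional. The CT call is not, because it prompts GP management even if only medicines are scored.
3. **The objective is wider than the letter.** The Synopsis asks how COPD assessment within screening affects management, and for that question these contacts belong to the package. That stands, and it is why the remedy is mainly one of interpretation. The Synopsis item on change in management, however, is tied to the recommendations sent to the GP.
4. **The Hawthorne allowance might cover some study contact.** Possibly, but the text ties it to inclusion and spirometry.

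A reader might also infer that the rule credits the letter when no GP has acted at all. The documents do not support that: in the CT-call route the action is management by the GP, and in the GP arm practice staff give the scan results. What may be missing is a response to the letter, not GP action. Nor is there a basis for a complaint about bias between arms, since one pooled proportion is tested and no arm comparison is planned for this outcome.

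**Conclusion.** The point holds in limited form. The test as planned cannot separate the letter from the other prompts the Protocol sets up, yet the interpretation offers the letter as the sole cause of an excess. The CT call is the firmest route, the review of GOLD B, C and D results is a second, and cessation support counts only if the scoring includes it.

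The sensitivity is appreciable: nine improvements above expectation give significance, and other trial care adding 2, 5 or 7 points would do so 16%, 61% or 85% of the time with no letter effect. These figures assume a true background of 10%, 200 participants, independent outcomes and a two-sided 5% test. The added points are illustrations; nothing in the Protocol shows how large the shift would be.

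The power statement is correct and needs no change.

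**What to change.** 1. In the statistical section on COPD assessment, state that an excess over 10% reflects the combined effect of the COPD assessment package (spirometry, CT report and study contacts, specialist-referral review, and letter) and is not attributed to the letter and recommendations alone. This is the essential change.
2. State that cessation support delivered under the trial's own procedures is not scored as an improvement in GP management. Report it separately, using the cessation medications and referrals already listed under Secondary outcomes.
3. Report the improvement proportion with Wilson limits for participants with and without a category 5 COPD finding on CT, and with and without a specialist referral. Label this descriptive: the groups may differ in disease severity, so the split does not isolate the letter.

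Restricting the scored items alone would not be enough, because the CT call and the specialist-referral review can prompt the very prescribing that remains scored.

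The cost is a few sentences and two descriptive tabulations from data the trial already holds. The conclusion becomes narrower and the observed proportion will probably be lower. Sample size is unaffected.

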| Objectives | 1. Determine the effectiveness of two invitation strategies for lung cancer screening; primary care vs central hub 2. Describe key lung cancer screening outcomes that are required to inform a potential national programme in NZ, including:    - Cancer detection rates    - Number and proportion of cancers detected by stage and grade    - Proportion of cancers detected that are surgically operable    - Scan positivity    - Types and rates of incidental findings. 3. Evaluate contextual implementation factors in order to optimise a future NZ screening programme. Including the confirmation of key assumptions such as:  - What % of not ‘never smoker’ Māori aged 55-74 in a general practice are eligible for lung cancer risk assessment - What % of people who are eligible for risk assessment agree to undergo risk assessment - What % of those undergoing risk assessment are eligible for lung cancer screening - What % of those eligible for lung cancer screening decide to proceed with screening - What % of those who decide to proceed with screening attend their appointment for screening - Usability of the risk assessment tool - Ability to implement blood biomarker analysis - Data collection and IT systems - Invitation materials - Consent processes - Results management   - Reporting in private community radiology clinic   - Standardised screen read and reporting   - Use of volumetric analysis   - Statistical integration of LDCT information with blood biomarker information   - Interpretation of results by providers and experience of providing results to participants and whānau   - Interface between primary and hospital care for positive screen management - Participant and whānau experience  1. Determine how COPD assessment within a lung cancer screening setting impacts the management of patients with COPD, including:  - Describing the prevalence and characteristics of COPD in those who undergo LDCT in this trial - Describing the primary care management of COPD - Describing any change in primary care COPD classification, recording of spirometry results and management following management recommendations to the participant’s GP - Describing the participant’s experience of COPD assessment and their views on whether it should be included in future lung cancer screening. |
| Test devices / procedures | Low-dose computed tomography  Spirometer  Blood sample biomarker analysis |

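### The COPD management test counts upward moves only, so an excess over 10% does not by itself show that management was better overall

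*Protocol*

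**What the plan says.** The rule is in the protocol under Sample size and statistical analysis, subsection COPD assessment. Management at baseline and 4 months after the report to the GP is graded by its consistency with the guideline recommendations for the patient's GOLD class: no, yes-partially or yes-fully. A patient is "classified as having had improved management if the assessment changes from either: no to yes-fully or yes-partially; or from yes-partially to yes-fully".

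The resulting proportion gets Wilson limits and is "tested for significance (one sample proportion test) versus the expected improvement proportion of 10" per cent. The benchmark stands for improvement expected anyway from ordinary GP care or a Hawthorne effect: "We expect this to seen in about 10% of patients". A significant excess is then said to be possibly due to the report and recommendations sent to the GP.

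The subsection has no category, deduction or test for a move from yes-fully to either lower level, or from yes-partially to no. The objectives are wider: the Synopsis lists "Describing any change in primary care COPD classification, recording of spirometry results and management", and the secondary outcomes list change in GP management without a direction.

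**The concern.** A rating taken twice can move both ways. The test sees one direction only, so its result is the same whether nobody worsened or as many worsened as improved.

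This is the sub-study's only test with a stated benchmark and power, and the only one used to infer that the GP reports may have worked. There is no control group, so the balance of upward and downward moves is one of the few internal checks available. The protocol also asks whether the care of patients already known to have COPD is optimised. For them, worsening is both possible and relevant.

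**Working it through.** **Inputs from the protocol.** n = 200, null proportion p0 = 0.10, alternative p1 = 0.17, stated power 85%. The level is given as "when the actual proportion is 17% or more (95% significance level", which I read as alpha = 0.05. Sidedness is not stated; two-sided is inferred because it reproduces the stated power.

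**Step 1: reproduce the stated power.**
- Null standard error: sqrt(0.10 × 0.90 / 200) = 0.02121.
- Standard error at 17%: sqrt(0.17 × 0.83 / 200) = 0.02656.
- Normal approximation: Phi((0.07 − 1.96 × 0.02121) / 0.02656) = 85.8%.
- Critical count: 28/200 gives z = 0.040/0.02121 = 1.89; 29/200 gives z = 0.045/0.02121 = 2.12. The test is therefore significant from 29 upward moves (14.5%). The Wilson lower limit gives the same cut-off.
- Exact binomial power: P(X ≥ 29 | n = 200, p = 0.17) = 85.0%.

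The stated 85% is correct.

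**Step 2: equal movement in both directions.** Downward moves do not enter the count, so the chance of significance is P(X ≥ 29 | 200, u), where u is the true upward rate, whatever the downward rate. With up = down = u, net change is zero.

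| u each way | Chance of a significant result |
| --- | --- |
| 10% | 2.7% |
| 12.5% | 22% |
| 15% | 61% |
| 17% | 85% |

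For example, 34 up and 34 down gives z = 0.07/0.02121 = 3.30.

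**Step 3: how far can patients fall?** Patients rated no at baseline cannot move down. The protocol's Background (COPD) cites two overseas programmes in which 50–70% of those with airflow limitation were undiagnosed. If a like share of the 200 starts at no (an assumption), 60 to 100 patients can worsen. Balancing 29 upward moves would then need 29/100 = 29% to 29/60 = 48% of them to worsen; balancing 34 would need 34% to 57%.

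Partial cancellation needs less. With 29 up and 20 down, net change is 9/200 = 4.5%, with standard error sqrt((0.245 − 0.045²)/200) = 0.0349 and 95% interval −2.3% to 11.3%. The 10% test is significant, while the net change is compatible with zero.

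**Step 4: rating error alone.** The protocol gives no error rate, so this step is illustrative. Suppose nothing truly changes, each rating has an independent chance e of falling on a neighbouring level (split evenly from the middle level), and patients are spread evenly over the three levels. The apparent improved share is e(1 − e) + e²/12.
- e = 10%: 9.1% improved, significant in 0.8% of trials.
- e = 15%: 12.9%, significant in 28%.
- e = 20%: 16.3%, significant in about 79%.

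Now let half the patients be truly at no with only 5% error, and the rest be split evenly over the other two levels with 20% error. The improved share is 0.5 × 0.05 × 0.95 + 0.25 × 0.17 + 0.25 × 0.16 = 10.6%, significant in about 5%. With no error in the no group it is 8.25%, significant in 0.2%.

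**Step 5: requiring a favourable net change as well.** With 17% truly moving up, both results are favourable (29 or more up, and the 95% interval for up minus down above zero) in 84% of trials at 5% down, 70% at 8% and 48% at 10%, by simulation. The present test alone gives 85%. At 17% each way, the joint rate is about 2.6%. The downward rates are assumptions.

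**The case against.** The strongest defence is that the test is valid for its literal question. The 10% null is itself a share of upward moves and already allows for ordinary upward drift under GP care. The protocol only says that an excess might be due to the reports, and it plans frequency distributions for ordinal data, so downward moves may well be tabulated. A 3x3 table is detail that a statistical analysis plan could supply. All of this stands. What it leaves open is that the protocol fixes both the tested event and the inference drawn from it, and neither takes account of worsening. The hedge about cause does not tell a reader that worsening was left out.

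Three stronger readings are tempting but unsupported:
- A reader might infer that rating noise alone will usually produce a significant result. That needs a high, uniform error rate. The documents give none, and the figure falls to about 5% or less when the bottom group is rated with little error.
- A reader might take this for the sub-study's only hypothesis test. Subgroup comparisons by GOLD class, age and gender are also planned.
- A reader might expect fully balanced movement to be the typical case. The floor at the lowest rating makes it demanding, and balanced movement at 10% or less passes at most 2.7% of the time.

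**Conclusion.** The point holds in a limited form. The rule as written makes the test blind to worsening: 29 upward moves out of 200 suffice, regardless of downward moves. At the protocol's own 17% alternative, a cohort with no net change passes as often (85%) as one in which nobody worsened. The power figure is right; the weakness lies in the endpoint and in what a significant result is taken to show.

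How much this matters in practice depends on quantities the protocol does not give. The chance of a significant result with zero net change runs from 2.7% to 85% as balanced movement rises from 10% to 17% each way. Under the simple rating-error model it runs from near 0% to about 79%. Partial cancellation is the likelier problem. The sub-study is secondary and uncontrolled, and the comparison of invitation strategies is not affected.

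**What to change.** Keep the existing test against 10%, and add to the same subsection:
- a worsened category that mirrors the improved one: yes-fully to yes-partially or no, and yes-partially to no;
- the full 3x3 table of baseline by 4-month ratings;
- improved minus worsened with a 95% confidence interval (or a paired test of upward against downward moves), reported beside the 10% test;
- a statement that an excess over 10% will be read as better management overall only if the interval for net change also lies above zero.

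Net change governs the interpretation here; it does not replace the 10% allowance, because it is compared with zero. Both ratings are already collected, so the cost is a short paragraph and one tabulation. The real downside is a more cautious conclusion if worsening is common, as step 5 of the working shows: little is lost at 5% worsening, but a good deal at 8–10%. The wording should be settled before the 4-month ratings are analysed, since a worsening rule added afterwards would be post hoc.
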